## Abstract

**Background:**

Medical training is very demanding and associated with a high prevalence of psychological distress. Compared to the general population, medical students are at a greater risk of developing a psychological disorder. Various attempts of stress management training in medical school have achieved positive results on minimizing psychological distress; however, there are often limitations. Therefore, the use of a rigorous scientific method is needed. The present study protocol describes a randomized controlled trial to examine the effectiveness of a specifically developed mindfulness-based stress prevention training for medical students that includes selected elements of cognitive behavioral strategies (MediMind).

**Methods/Design:**

This study protocol presents a prospective randomized controlled trial, involving four assessment time points: baseline, post-intervention, one-year follow-up and five-year follow-up. The aims include evaluating the effect on stress, coping, psychological morbidity and personality traits with validated measures. Participants are allocated randomly to one of three conditions: MediMind, Autogenic Training or control group. Eligible participants are medical or dental students in the second or eighth semester of a German university. They form a population of approximately 420 students in each academic term. A final total sample size of 126 (at five-year follow-up) is targeted. The trainings (MediMind and Autogenic Training) comprise five weekly sessions lasting 90 minutes each. MediMind will be offered to participants of the control group once the five-year follow-up is completed. The allotment is randomized with a stratified allocation ratio by course of studies, semester, and gender. After descriptive statistics have been evaluated, inferential statistical analysis will be carried out with a repeated measures ANOVA-design with interactions between time and group. Effect sizes will be calculated using partial η-square values.

**Discussion:**

Potential limitations of this study are voluntary participation and the risk of attrition, especially concerning participants that are allocated to the control group. Strengths are the study design, namely random allocation, follow-up assessment, the use of control groups and inclusion of participants at different stages of medical training with the possibility of differential analysis.

**Trial registration:**

This trial is recorded at German Clinical Trials Register under the number DRKS00005354 (08 November 2013).

## Background

### Stress and psychological morbidity in medical school

Scientific research indicates that medical training is associated with a high prevalence of psychological distress. The occurrence of burnout symptoms among medical students is reported to range from 45% to 71% [1], and numerous data suggest an increase in psychological morbidity. This becomes evident in a higher symptom load for mental disorders when comparing medical students with an age-matched control sample. Medical students at different stages of their training scored significantly higher on scales of the Patient Health Questionnaire (PHQ) such as ‘major depressive syndrome’ or ‘other anxiety syndromes’ [2]. A poorer mental health, measured by the ‘Short Form-12 Health Survey’ (SF-12), is also reported for medical students in their first, second and third year of studies compared to a reference sample [3]. These findings of a high level of overall psychological distress in medical students is confirmed by a variety of scientific studies and summarized in a review of the literature [4].

Studies providing data that enable an assessment of the psychological morbidity in medical training in contrast to other courses of studies are scarce and results differ. Aktekin *et al*. [5], for example, revealed that with the General Health Questionnaire (GHQ), a higher percentage of medical students scored above threshold in comparison to students of economics and physical education. However, according to Dahlin *et al*. [6], the prevalence of mental health problems in need of treatment and the frequency of ‘help seeking’ did not differ between medical and business students. More research is needed investigate whether medical students experience more stress than other high-achieving student populations.

Nevertheless, a high level of perceived medical school stress is strongly associated with psychological problems [7-9]. For example, high ratings on a stress inventory within a cohort of medical students are positively correlated with depressive symptoms [10]. Consequently, there is a demanding risk of developing mental health problems in later professional life [11]. The competency and professionalism of physicians may be affected by poor mental health, and consequently, the treatment of patients may be impaired [12]. Therefore, health promotion and prevention programs of psychological symptoms during medical school seem necessary and beneficial for both physicians and patients.

### Intervention programs

In a review of the literature, Shapiro *et al*. [13] discovered over 600 articles discussing the need to address the stress of medical education. However, only 24 studies reported intervention programs. A decade later, the number of stress-management programs has not increased significantly [14,15], and to our knowledge, no study of a prevention program in German medical schools has yet been published. There has been a variety of stress-management programs offered in medical schools aimed at relaxation training, mindfulness-based stress reduction, self-hypnosis, educational discussion groups on self-care, support groups, mentoring programs and others [16-21]. A review of the literature makes it apparent that intervention programs are helpful [22], and the students who completed the trainings were in favor of the programs being offered regularly [13]. This impression is confirmed by Yusoff *et al*. [14], who reviewed 23 studies of stress-management programs. Regardless of the duration of training, they all reported positive outcomes on several areas related to health, such as improved psychological health, quality of life or increased awareness of stress and stress management. Despite achieving good effects, the studies are reported to have limitations, and the necessity of using rigorous scientific method is needed [13]. According to Yusoff *et al*. [14], only one in 23 studies used a random sampling method in selecting participants, 13 studies had control groups and only seven randomly assigned participants to control and intervention groups. Furthermore, follow-up assessments to evaluate the prevention effects of the interventions are mostly missing or the intervals are short [13-15].

In order to address these limitations, we use a randomized controlled trial that implies an allocation of the participants to three groups (experimental treatment, standard treatment and control without treatment). Given that nothing is known about the most efficient point in time to offer stress-management training, we examine medical students at two different stages of medical training. Additionally, we expect our research design to enable us to determine which of the two interventions work best for whom.

In order to address the psychological health of medical students, we have developed a mindfulness-based stress prevention training tailored to the needs of students in medical education. Following the concept of dialectical behavior therapy developed by Linehan [23], we combine acceptance strategies as described below (concept of mindfulness) with change strategies (contents of cognitive behavioral therapies). This combination enables the students to react to stressful conditions by modifying the situation, adapting their judgement mechanisms, or otherwise to meet these conditions with acceptance. Therefore, the development of the training is based on scientifically proven concepts of stress reduction like Kabat-Zinn [24], Lehrhaupt and Meibert [25], Hassed [26], Linehan [27] (German adaption, Bohus and Wolf [28]) and Kaluza [29].

### Concept of mindfulness and proof of efficacy

Mindfulness is an ancient Buddhist practice that became popular in the Western culture by the work of Jon Kabat-Zinn. It is characterized by ‘paying attention in a particular way: on purpose, in the present moment, and nonjudgementally’. [24]. Mindfulness therefore includes ‘paying attention to our thoughts and emotions in the present moment’ [30] and changing our attitudes towards them. This is of high relevance, given that perception of stress often originates in stressful thoughts about the future or ruminations about the past [30]. The integration of this capacity of nonevaluative moment-to-moment awareness into everyday life may function as a coping resource for dealing with difficult emotions [24] and the experience of stress. Mindfulness-based stress reduction (MBSR) is a group-intervention program developed by Jon Kabat-Zinn, which has been proposed as an approach to address a wide spectrum of clinical populations as well as nonclinical groups. The success of this approach becomes apparent in a meta-analysis that showed medium effect size of 0.5, including 20 reports of controlled and observational investigations [31].

In addition, mindfulness practice has already been successfully employed in medical school [16,17,21,32,33]. The existing data show good results from a before and after comparison concerning improvement on scales such as the perception of stress, depression, anxiety or quality of life. As mentioned above, follow-up data to evaluate the prevention effects is largely absent; only Warnecke *et al*. [32] found that the positive effect of mindfulness treatment was maintained for 8 weeks post-trial. Therefore, our investigation aims at indicating significant changes even after one year post-trial.

Positive effects of mindfulness-oriented interventions on psychological health of clinical and nonclinical samples have been repeatedly confirmed [34,35]. There seems to be a wide variety of health promoting aspects due to mindfulness training beyond the results already mentioned. For example, empirical literature indicates positive changes in psychological constructs such as ‘self as a source of control’ [36] or ‘satisfaction with life’ [37]. In contrast to relaxation training, mindfulness meditation seems to be specifically effective in reducing distress by positively influencing distractive and ruminative thoughts and behavior [21]. As rumination has been considered a risk factor for a number of psychological disorders [38], mindfulness training gains importance as a prevention strategy leading to a reduction in rumination by increasing metacognitive awareness [39]. Furthermore, correlation studies refer to associations between trait mindfulness and aspects of psychological health such as self-esteem [40], empathy [41], sense of autonomy [42] or optimism [42].

### Risk factors

Before developing our stress prevention training, we reviewed literature to obtain information regarding risk factors associated with psychological morbidity in medical education. We intended to develop a program based on findings of specific risk factors to increase its prevention effect and to affect the special needs of medical students. Unfortunately, the number of prospective studies is limited and often the results have not been confirmed. In addition, limitations are inherent in the research design or statistical analysis, for example, no multivariate aspects. The existing empirical literature indicates that deterioration of psychological health of medical students is associated with some of the following factors: study related stressors [9], exposure to life events [8,43], personality traits such as impulsivity [44], maladaptive perfectionism [45], external locus of control [46], performance-based self-esteem [44] and coping mechanisms such as wishful thinking [46]. Scores were generally low in active coping [9] or avoidant coping strategies [47]. In a longitudinal investigation [48,49], self-criticism as a personality variable was discovered to be a strong predictor of stress symptoms over a period of 10 years. Medical students were repeatedly examined from their fourth year of study up to the time when they were working as general practitioners. Remarkably, the hours worked in the past week did not significantly correlate with current stress levels, but the degree of self-criticism as students did.

In order to gain information on whether stress prevention training is able to influence these risk factors, we will obtain these factors by psychometric measures.

### Primary and secondary aim

The primary aim of this research is to examine the effectiveness of a mindfulness-based stress prevention training for medical students (MediMind). It is hypothesized that MediMind will be more effective in the reduction of stress and prevention of psychological morbidity as a standard treatment and more effective than a control condition. The evaluation will be based on an interaction-related stress concept [50], in which stress is defined as a nonmatch between requirements and the resources available to a person according to the transactional model of stress and coping by Lazarus [51]. Therefore, we expect MediMind to have a beneficial effect on the experience of stress and coping strategies as primary and co-primary outcome. Furthermore, as secondary outcome we expect MediMind to have a preventive effect on psychological morbidity that will be visible only after reviewing the follow-up surveys.

The secondary aim of this research is to examine the effect of MediMind on risk factors associated with psychological morbidity in medical students compared to a standard treatment and a control condition. It is expected that MediMind has a beneficial effect on rumination as a coping style in response to dysphoric mood and personality traits like impulsivity, perfectionism, self efficacy expectations, locus of control and self-esteem. In this context we expect MediMind to have a positive effect on satisfaction with life of the participating medical students. Additionally, a measure of mindfulness will be included to assess the expected improvement in mindfulness by participation in MediMind.

## Methods/Design

### Trial design

This is a prospective, randomized, controlled trial, involving four assessment time points (baseline, post-intervention, one-year follow-up and five-year follow-up) and three groups (experimental treatment, standard treatment and control without treatment). Participants are a self-selected group that will be assigned randomly to either the experimental, standard or control group. The longitudinal design will allow the evaluation of the short- and long-term effects of the intervention. Figure 1 shows the overall design of this project. All study procedures, written information and consent forms received approval from the local ethics committee (Landesärztekammer Rheinland-Pfalz, file number: 837.380.13/9065-F) and the University Medical Center data protection official. To report this randomized controlled trial we made use of the CONSORT guidelines [52,53].

**Figure 1 Fig1:**
[figure not shown]
‘**Study design’.**

### Participants and recruitment

Participants are medical students in the second and eighth semester. In addition to students of human medicine in the preclinical cohort, dental students will be included. Their curriculum and learning environment is nearly analogous to medical students in the preclinical semesters. Students that fit these eligibility criteria and study at the Johannes Gutenberg-University Mainz form a cohort of approximately 420 students in each academic term (second semester: 50 dental and 200 medical students; eighth semester: 170 medical students). It is expected to recruit a minimum of 30% of the possible participants according to literature [17] each semester resulting in an initial sample size of 126 participants. Over the course of time between baseline and five-year follow-up we expect a maximum dropout rate of 50% leading to a final sample size of 189 participants with participants of 3 semesters. The optimal sample size was calculated through analyzing and integrating related publications [16,17,21] via effect sizes (F-values respective η-square-values, Cohen’s d and Λ for multivariate approaches) with G*Power [47]. A synopsis of needed sample sizes for the different articles and different outcome measures within the articles was constructed and evaluated. This resulted in an approximate value of the minimum total sample size of 126 participants at five-year follow-up for valid analysis of secondary outcome.

Students are informed about the project via e-mail, and the Department of Medicine student body shares information on their social network. Additionally, our team introduces the study design and the opportunity for participation at lectures. At that time, we hand out written information and informed consent. Students who return the signed informed consent are introduced to the baseline assessment. They have the choice of either filling out the questionnaire as a paper-and-pencil version or completing an online version. In addition to the signed informed consent, the completion of the baseline assessment is a requirement of becoming assigned to the study groups.

### Randomization

Following baseline assessment, the participants are allocated to one of the three conditions: MediMind, Autogenic Training or control group. Participants with informed consent are stratified randomized initially by course of study (medical versus dental), semester (2nd or 8th) and gender. This was due to control for potential confounding effects and secure homogenous distribution among groups. The randomization to the groups will be with an allocation ratio 2 (MediMind) : 2 (Autogenic Training) : 1 (control group), for ensuring a maximum power for analysis between MediMind and Autogenic Training. After stratification the groups are randomized by drawing lots using the aforementioned allocation ratio. The randomization to the groups will be done by an independent member of institute not involved in this project, ensuring that trainers and recruiters are kept blind to the allocation of each participant. Treatment participants are openly informed into which group they are allocated. Additionally, participants in the control group will be informed of their status and the opportunity to attend MediMind when data collection is completed after five years. Over these five years participants of the control group get no intervention but are invited to fill out the questionnaires at each of the four assessment time points.

### Trainers

Interventions will be presented by four trainers who are qualified and skilled in imparting the manualized contents of the experimental and standard treatment group to students. Two clinical psychologists with additional training in psychotherapy and experience in leading group psychotherapy are chosen for the experimental group (MediMind). They have personal experience in mindfulness meditation and attended external training. They are advised in conducting the training and all details concerning the implementation of the training are available in a comprehensive script. The standard treatment group (Autogenic Training) is presented by two trainers: a sports scientist certified as a trainer of Autogenic Training with long-term experience in teaching these techniques to students and a clinical psychologist with additional training in psychotherapy and Autogenic Training. The treatment of Autogenic Training is also based on a comprehensive script.

### Intervention

Both treatment groups meet over a period of five weeks with a weekly session of 1.5 hours. Within both groups further information and assignments concerning the topics of each training session are provided by an accompanying booklet or handouts.

Based on experiences with a pilot run of the intervention training (MediMind), there should not be more than 15 participants in each training group.

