Module III: The manner in which cognitive judgment mechanisms influence one’s own experience is imparted to the participants. For a better understanding, we use a stress induction exercise and study everyday examples in order to derive how one’s own appraisal can have a stress heightening influence. These dysfunctional cognitive judgement mechanisms (errors in reasoning) are discussed by the participants in small groups and then presented to the group. Prior to the next session, an assignment will enable the participants to identify errors in reasoning and practice the use of functional reevaluation. An audio CD with a breathing meditation is handed out to the participants to support the practice of mindfulness meditation.

Module IV: This session deals with personal standards and assumptions that have a causal influence on cognitive judgment mechanisms and thus may exacerbate the experience of stress. With the help of everyday life examples, the idea of ‘stress exacerbating settings’ is conveyed to the participants and they can test themselves to determine their core beliefs. It will then be discussed as to which of these core beliefs exacerbate the experience of stress and which can also be helpful. An educational film that emphasizes some specific assumptions in medical education is used to question them critically. Another focus is to highlight how the stress heightening effect of individual core beliefs can be mitigated. In an exercise participants practice coping with functional stress exacerbating settings in the form of various experiments that are grounded on both mindfulness-based and cognitive behavioral therapy.

Module V: The last module focuses on stress-tolerance skills and the concept of radical acceptance [23]. First, the participants determine the characteristics of individual high-tension situations, from which the necessity for and effectiveness of stress tolerance skills is derived. These are then presented to the group and experienced through exercises. As a last resort, to cope with tense situations that can neither be influenced by their external circumstances nor by stress-tolerance skills, the concept of radical acceptance is developed and applied in a practical exercise. At the end of the training, participants draw conclusions and compile worksheets defining what they learned and what they want to remember in the future.

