### Statistical methods

Descriptive statistics on study population will be calculated for each group at baseline. Means and standard deviations on primary, co-primary, secondary outcome and additional measures will be presented at baseline, post intervention and at the two follow-up time points for each group. A two-folded approach according to Tabachnik and Fidell [75] is used to address missing data. Initially, a Completer-Analysis with a sample of complete data-sets of each person is evaluated. Secondly, an Intent-to-Treat-Analysis with a Last-Observation-Carried-Forward-Method will be applied to check for differences and possible drop-out-effects. The null hypothesis will be rejected at the cut-off of 5% (α-level), therefore a *P* value ≤ .05 will be applied. To evaluate all group x time interactions in one model, we will use an explicatory MANOVA with primary, co-primary and secondary outcome. We expect differential time x group effects on secondary outcome at the one year/five year follow-up after post-intervention assessment. Therefore, this preliminary analysis will be called ‘explicatory’. For confirmatory analysis following the assumption that primary and co-primary outcome are separate hypothesis, both hypotheses will be tested in separate repeated-measures ANOVA’s with the factorial structure group (MediMind, Autogenic Training and control group) x time. The hypothesis will be evaluated through testing interaction effects. Orthogonally constructed comparisons are then used to check for pairwise differences. If needed, Holm-Bonferroni corrected pairwise comparisons will be used [76]. Additionally post-hoc sub-group comparisons (sex, semester, cohort) will be conducted to analyze data sets furthermore.

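### If training groups affect outcomes, the arm-by-time ANOVA gives P values that are too small, most of all for MediMind versus Autogenic Training, because it has no training-group term

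*Protocol article*

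**What the plan says.** Under Randomization, students are allocated individually in a 2:2:1 ratio to MediMind, Autogenic Training and control. The ratio is justified by power for the comparison of the two trainings. Of the third arm the section says that "participants of the control group get no intervention but are invited to fill out the questionnaires".

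Under Intervention, "Both treatment groups meet over a period of five weeks with a weekly session of 1.5 hours", and "there should not be more than 15 participants in each training group". Under Trainers, "Interventions will be presented by four trainers", two for each active arm. The MediMind description includes joint work: in Module III, dysfunctional judgements "are discussed by the participants in small groups and then presented to the group". The Autogenic training section gives each session a closing discussion.

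Under Statistical methods, the primary and co-primary outcomes are each tested in a separate repeated-measures ANOVA "with the factorial structure group (MediMind, Autogenic Training and control group) x time". The hypothesis is judged by the interaction, followed by orthogonal or, if needed, Holm-Bonferroni pairwise comparisons. Here group means trial arm. No factor for training group appears. The sample-size paragraph states no intraclass correlation or design effect, and the Discussion does not list clustering as a limitation.

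**The concern.** Students who sit through the same five sessions share a trainer or trainers, discussion partners and group dynamics. If these influence stress or coping, outcomes within a training group are correlated after the intervention. The repeated-measures structure handles correlation within a student over time, but not between students in one training group.

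The clustering would exist in two arms and be absent in the third (a partially nested design). A model without it uses standard errors that are too small for any contrast involving a trained arm. The error is largest for MediMind versus Autogenic Training, where both sides are clustered. That is the contrast the allocation ratio was chosen to serve, and superiority over the standard treatment is part of the primary hypothesis. What is at stake is a claim of superiority at a real error rate above the stated 5%. Holm-Bonferroni correction deals with multiplicity and does not repair the standard errors.

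**Working it through.** **The plan's own figures.** Recruitment per term is 420 × 0.30 = 126. Three terms give 378, and 50% dropout leaves 189, as stated. The minimum of 126 at five years cannot be reproduced, because the article gives neither the effect size nor the power behind it.

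**Inputs from the protocol.** Individual randomisation 2:2:1; groups of at most 15; untreated controls; α = 5% (taken as two-sided); dropout up to 50%.

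**Derived layout.** Per term, each active arm receives 126 × 0.4 ≈ 50 students. With a cap of 15 that needs 4 groups of about 13. Three terms give 12 groups (about 151 students) per active arm and 378 × 0.2 ≈ 76 controls. After 50% dropout about 6 remain per group.

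**Assumption.** The documents give no intraclass correlation (ICC). I use 0 to 0.10, defined on the change from baseline.

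**Formulas.**
- Design effect in a clustered arm: DE = 1 + (m − 1) × ICC.
- Ratio of true to naive standard error, both arms clustered: r = √DE.
- MediMind versus control, one arm clustered: r = √[(DE/151 + 1/76) / (1/151 + 1/76)].
- Only one of the two active arms clustered, equal sizes: r = √[(DE + 1)/2].
- True level of a nominal 5% test: 2 × [1 − Φ(1.96/r)].

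Example: m = 13 and ICC = 0.05 give DE = 1 + 12 × 0.05 = 1.60, r = 1.265, 1.96/1.265 = 1.55, level 12.1%.

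| ICC (assumed) | DE, m = 13 | MediMind vs Autogenic, both clustered | Same contrast, one arm clustered | MediMind vs control | MediMind vs Autogenic, m = 6 |
|---|---|---|---|---|---|
| 0 | 1.00 | 5.0% | 5.0% | 5.0% | 5.0% |
| 0.01 | 1.12 | 6.4% | 5.7% | 5.5% | 5.6% |
| 0.02 | 1.24 | 7.8% | 6.4% | 5.9% | 6.2% |
| 0.05 | 1.60 | 12.1% | 8.6% | 7.4% | 8.0% |
| 0.10 | 2.20 | 18.6% | 12.1% | 9.8% | 11.0% |

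The last column describes completers at five years. The planned last-observation-carried-forward analysis keeps all students, so group size does not shrink there.

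**Does it reach the planned test?** I simulated null trials with a three-arm F test on change scores, which is the group-by-time interaction for two time points. With 12 groups of 13 per active arm and 76 controls, it rejected in about 7%, 11 to 12% and 17 to 18% of trials at ICC 0.02, 0.05 and 0.10. So the overall interaction test is affected, as well as the pairwise contrasts.

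**Would an ordinary random intercept help?** Baseline is measured before assignment, so no training group exists then. Write the training-group effect as u_g. If the model adds u_g to every assessment, then in (post − baseline) it becomes u_g − u_g = 0. It drops out of the time contrast, and with balanced data the interaction standard error is unchanged. The real effect is present only after baseline, so the model must place it there.

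**The case against.** Much of the opposing case stands and limits the point.

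- **The effect is conditional.** With individual randomisation, clustering arises only if training groups themselves influence outcomes. At ICC 0 the planned test is valid; at 0.01 the level is only about 6%. A reader might infer that the P values are certainly too small. The documents give no ICC and do not support that.
- **Equal clustering is an assumption.** Interactive work is described mainly for MediMind. Autogenic Training is largely self-instructed, though each session has a closing discussion. The cap of 15 comes from a MediMind pilot, although it is worded for every training group. The article does not say whether an arm's two trainers co-lead or divide the groups.
- **Two tempting extensions fail.** A reader might add that confidence intervals are too narrow, but the article plans P values and partial η², not intervals. A reader might also infer unequal residual variance; partial nesting adds a between-group component and says nothing about the residual.
- **The figures are not the plan's exact error rate.** They concern single contrasts of a change score. If the ICC is instead set at 0.05 on the post score, the ICC of the change is 0.05/[2(1 − ρ)]. That is 0.036 at a pre-post correlation ρ of 0.3 and 0.083 at ρ = 0.7, giving levels of about 10% and 17%.
- **The article is condensed.** A fuller protocol could contain more terms. But this article states its confirmatory model and its factors, and that stated model assumes independent students. The point therefore concerns a choice made here and not a detail left open.

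**Conclusion.** The point holds in conditional form. The stated confirmatory model has no means of detecting or allowing for correlation within training groups, although two of the three arms are taught in such groups. If the ICC is positive, the group-by-time P values are too small. Over an assumed ICC of 0 to 0.10 with about 13 per group and equal clustering, the true level runs from 5% to about 19% for MediMind versus Autogenic Training and from 5% to about 10% for MediMind versus control. With about 6 completers per group at five years, the first contrast runs from 5% to about 11%. If only one active arm clusters, the upper figure at 13 per group falls to about 12%.

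That the term is missing is certain on the text; the size is not, because it rests on an ICC and a pre-post correlation that the documents do not give. The trial design remains sound. The analysis should be changed, because the affected contrast is the one the design was built to favour.

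**What to change.** 1. Record each student's training group. Recruitment is described as ongoing, and membership may be hard to reconstruct after five years.
2. Replace the confirmatory ANOVA by a partially nested mixed model in which the training-group effect acts on post-baseline assessments in the two active arms only. Either use a training-group-by-time random effect, or model post-baseline scores adjusted for baseline with a random training-group effect. A time-constant random intercept alone is not enough.
3. Use Satterthwaite degrees of freedom, and optionally allow residual variance to differ by arm.
4. Report the estimated ICC. Describe results by trainer without modelling trainer as random, since two per arm are too few.

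Cost: the contrasts that involve an active arm become somewhat less precise if the ICC is above zero. The planned partial η² no longer follows from the confirmatory model. It must either be kept as a descriptive figure from the planned ANOVA or be replaced by a model-based effect size. No additional outcome assessments are needed.
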